### Criteria for discontinuing or modifying allocated interventions {11b}

(1) The presence of serious adverse events that doctors believe should lead to termination of trial participation, such as severe internal or external root resorption and tooth fracture; (2) poor clinical compliance; and (3) withdrawal of consent for study participation by the patient.

### Strategies to improve adherence to interventions {11c}

During the study, patients will receive text messages and phone calls to remind them of their appointments for treatment and follow-up visits and to answer the questionnaires.

### Relevant concomitant care permitted or prohibited during the trial {11d}

Patients are prohibited to take any anti-inflammatory or antibiotic medication during their participation at this research study.

### Provisions for post-trial care {30}

At the end of the study, patients will be proposed to continue their long-term oral follow-up at the Brazilian Unified Health System in the cities of Itabuna, in the State of Bahia, and in Goiânia, in the State of Goiás, Brazil.

### Outcomes {12}

All the steps of clinical examination will be carried out by the two examiners responsible for the study. Imaging evaluation will be done by other 2 specialists in Endodontics and 1 radiologist. All are with at least 15 years of experience.

Assessments will also be carried out at 6 (IOPAR), 12 (IOPAR), and 24 (CBCT) months for analysis of the tissue repair process. The therapeutic effect evaluation criteria are the following: (1) success: after RCT, the tooth should be asymptomatic, without fistula, without pain on percussion and palpation tests, without edema and in normal chewing function, radiographically in the process of periapical lesion regression from the first assessment (time point) at 06 months, and fully repaired after 2 years with confirmation through CBCT; and (2) failure: after RCT, the tooth is symptomatic, with symptoms of apical infection such as pain and fistula. The radiographic examination demonstrates the absence of decreased apical lesion or an enlarged apical lesion [22, 23].

#### Primary outcome measures

##### Healing of periradicular lesions by radiographic findings according to periapical index (PAI)

The periapical index (PAI) is a structured scoring system for categorization of radiographic features of apical periodontitis. It is based on a visual scale of periapical periodontitis severity and was built upon a classical study of histological-radiological correlations. It is a 5-point ordinal scale as listed below: (1) normal periapical structures, (2) small changes in bone structure with no demineralization, (3) changes in bone structure with some diffuse demineralization, (4) apical periodontitis with a well-defined radiolucent area, and (5) severe apical periodontitis, with exacerbating features [22, 23].

#### Secondary outcome measures

##### Patient’s postoperative pain using a questionnaire

Patients will answer a questionnaire for the analysis of postoperative pain, through the analog pain scale, in an interval of 24h, 48h, and 72h and 7 days: (0) no pain, (1) mild, (2) moderate, (3) severe, and (4) intense (Fig. 2).

**Fig. 2 Fig2:**
[figure not shown]
Patient’s postoperative pain—pain scale (VAS) questionnaire

##### Patient’s preference regarding the number of clinical visits using a questionnaire

For the data on the patient’s preference regarding the number of clinical visits to be planned for the conduction of endodontic treatment, patients will answer their preferences according to hypothetical conditions described in a previously delivered questionnaire: (1) single visit, (2) two (or multiple) visits, and (3) no preference (Fig. 3).

**Fig. 3 Fig3:**
[figure not shown]
Questionnaire on the patient’s preference regarding the number of clinical visits to be planned for the conduction of endodontic treatment

##### Patient’s post-treatment satisfaction using a questionnaire

A post-treatment satisfaction questionnaire will be applied to patients undergoing clinical interventions in a single visit and multiple visits, using the following criteria: (5) fully satisfied, (4) satisfied, (3) neither dissatisfied nor satisfied, (2) dissatisfied, and (1) totally dissatisfied (Fig. 4).

**Fig. 4 Fig4:**

Patient’s post-treatment satisfaction degree questionnaire

### Participant timeline {13}

The study timeline is summarized in Table 1.

**Table 1 Tab1:**
[figure not shown]
Study timeline: enrolment, interventions, and assessments

**Group 1-RCT-SV*, root canal treatment in a single visit; *group 2-RCT-TVWD*, root canal treatment in two visits with intracanal dressing; *group 3-RCT-TVWOD*, root canal treatment in two visits without intracanal dressing

### Sample size *{14}*

The determination of the sample size will be performed sequentially, with a minimum of 210 statistical units (teeth) to be recruited in the first stage, and the second stage of recruitment will be performed if the selection is insufficient to clinically and radiographically identify valid cases. This sampling will also allow the adjustment of the sample size for the intra-subject correlation of statistical units (teeth). In the first stage, 150 adults aged 18 to 60 years, with at least one tooth diagnosed with asymptomatic apical periodontitis and periradicular lesion with a diameter between 1 and 5 mm, will be recruited.

## Sample size and statistical methods

### Sample size details

The required sample size was calculated based on the preliminary outcome parameter of success, in a sequential approach, with each clinical case (tooth) serving as the statistical unit. Clinical studies that allow us to estimate, by means of CBCT, the repair index (complete absence of periapical radiolucency), therefore the success, after endodontic treatment of teeth with apical periodontitis and periradicular lesion, state that it is necessary to have a follow-up of at least 2 years to determine the success or failure of the treatment [22, 23]. After the first year of follow-up, post-endodontic treatment, it is still possible to observe the presence of periapical radiolucency in 52 to 84% of cases [1, 24, 25]. The sample will consist of 210 mandibular molars (first or second molars), based on statistical sample calculation, considering a power of 80%, an alpha value of 0.05, and an effect size of 20%. All patient characteristics at the beginning of treatment, such as age, gender, lesion size, among others, will be considered in the statistical analysis, in order to confirm the randomization of groups and the possible confounding effect of these characteristics.

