## Assignment of interventions: allocation

### Sequence generation {16a}

Assignments will be prepared by the statistician author of this study ([name]) prior to the trial start. A total of 150 patients (210 teeth) will be recruited and divided into 3 groups at a ratio of 1:1:1, namely, the RCT in a single visit, RCT in two visits with intracanal dressing, and RCT in two visits without intracanal dressing.

Randomization and allocation will be performed before all the clinical procedures.

First, a list of numbers from 1 to 210 will be created, each of the number represents one participant, then the list of numbers was assigned randomly following simple randomization procedures, by using Excel 2019 (Microsoft, Redmond, WA, USA) into three groups of 50 participants (70 teeth) each. Eventually, two columns in the spreadsheet are used, the first column contains the number of the participant (teeth) and the second contains the group to which the participant (teeth) is allocated, determined solely by the software.

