#### Baseline analysis

The three groups will be similar in terms of disease type and periapical lesion size.

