#### Main outcome analysis

The inter-group comparison of success rates will be analyzed using the Kruskal-Wallis test at 5% of the level of significance. For the missing data, the last observation carried forward (LOCF) method will be adopted to fill the validity analysis.

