### Methods for additional analyses (e.g., subgroup analyses) {20b}

N/A. No additional analyses are planned.

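### Baseline characteristics are to be used to confirm the randomisation and examine confounding: the first cannot be done, and the second has no place in the stated analysis

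*Protocol article*

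**What the plan says.** Four places in the protocol article bear on this.

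- **Sample size details.** The variables are "All patient characteristics at the beginning of treatment, such as age, gender, lesion size, among others". They "will be considered in the statistical analysis, in order to confirm the randomization of groups and the possible confounding effect of these characteristics". No baseline test, threshold, selection rule or adjusted model is named.
- **Main outcome analysis.** "The inter-group comparison of success rates will be analyzed using the Kruskal-Wallis test at 5% of the level of significance". This is the only test named for the primary endpoint.
- **Methods for additional analyses {20b}.** "No additional analyses are planned". Section {20c} adds sensitivity analyses, but these concern missing data, not covariates.
- **Baseline analysis.** "The three groups will be similar in terms of disease type and periapical lesion size". Sequence generation {16a} says the list was "assigned randomly following simple randomization procedures, by using Excel 2019", and no stratification factor is named.

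**The concern.** The sentence under Sample size details gives the baseline data two jobs, and each has a problem.

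The first job is to confirm that randomisation worked. Under a random list, differences between arms at baseline arise by chance. Finding some does not show that the allocation failed, and finding none does not show that it was sound. The Baseline analysis section has a related fault: it asserts similarity in advance, which simple randomisation without stratification cannot guarantee.

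The second job is to deal with possible confounding. That implies an analysis using covariates, yet the primary test cannot carry any and nothing further is planned. The three statements cannot all be followed. Either the confounding step is never carried out, or it is carried out by an unnamed method after the data are in, and nothing says how its result ranks against the unadjusted one.

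At stake is how the primary result is read. If lesion size or site looks uneven between arms, the report could carry an unadjusted and an adjusted answer to the same question with no rule set beforehand for which one counts. The plan also forgoes a covariate-adjusted primary comparison that variables already recorded would allow.

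**Working it through.** **Inputs.** From the protocol: 210 teeth in 150 patients, allocated 1:1:1, so 210 / 3 = 70 teeth per arm; a 5% significance level; characteristics named as age, gender and lesion size, with the list left open. The 210 cannot be reproduced, because no base success rate, effect scale or sidedness is given; this point does not dispute it. Assumed, because the protocol does not give them: the number of characteristics, that each would be tested at 5%, and how strongly they predict repair.

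**Step 1: can the stated parts be carried out together?**

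| Section | What it requires |
|---|---|
| Sample size details | Baseline characteristics enter the analysis, partly for confounding |
| Main outcome analysis | One Kruskal-Wallis test across three groups, with no covariate term |
| {20b} | Nothing further planned |

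A Kruskal-Wallis test uses only the outcome and the group label. On a success/failure outcome it equals (N − 1)/N times the Pearson chi-square, here 209/210, so it is in effect an unadjusted comparison of three proportions. If the confounding step belongs to the main analysis, the named test cannot do it. If it is an additional analysis, {20b} excludes it.

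**Step 2: how often would a sound randomisation look unbalanced?** With k independent characteristics each tested at 5%, the chance of at least one apparent imbalance is 1 − 0.95^k:

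- k = 3: 1 − 0.857 = 14%
- k = 6: 1 − 0.735 = 26%
- k = 10: 1 − 0.599 = 40%

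These figures apply only if such tests were run. The protocol names none.

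**Step 3: what would covariate handling do to the 5% level?** Two null simulations with 3 × 70 teeth and no treatment effect; neither models clustering of teeth in patients.

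*Simulation A.* Three covariates, 12,000 runs per setting, F tests on the binary outcome. Covariate effect is the assumed log-odds per SD of the strongest covariate; a second covariate had 0.3 times that effect and the third had none.

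| Handling | Effect 0 | Effect 0.5 | Effect 1.0 |
|---|---|---|---|
| Unadjusted | 4.9% | 5.1% | 4.7% |
| All three covariates fixed in advance | 5.0% | 4.9% | 5.0% |
| Only covariates with baseline p < 0.05 | 5.0% | 4.9% | 4.4% |
| Smallest p of the 8 possible covariate sets | 5.8% | 7.0% | 7.8% |

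*Simulation B.* Six covariates with log-odds 0.9, 0.4, 0.2, 0, 0 and 0 per SD, logistic outcome. Unadjusted: 5.4%. Smallest p over 10 covariate sets: 9.7% (1,500 runs, standard error √(0.097 × 0.903 / 1,500) = 0.8 points). Adjusting only for covariates with baseline p < 0.05: 4.2% (3,000 runs).

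Adjusting on observed imbalance alone does not inflate the error. Only free choice of the most favourable model does, to about 6% to 10%.

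**The case against.** A reader might infer that the protocol plans to choose covariates from observed imbalance, and so leaves the primary result open to selection after the data are seen. The documents do not support this. The sentence says all characteristics will be considered; it does not say they will be picked by how uneven they look. The Main outcome analysis section fixes one unadjusted test, and {20b} read plainly restrains the analyst. No section plans a choice among several models, so the 9.7% describes a search the protocol does not propose. That objection stands, and it sets the limit of this point.

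A second objection is that a baseline comparison has some use here. Randomisation precedes all clinical procedures, yet teeth in which patency is not obtained are excluded, which may become known only during treatment. Investigators also open the envelopes and have access to the list. Arms could therefore differ for reasons other than chance. This stands in part and supports a descriptive table by arm. A worrying pattern would call for an inquiry into allocation and exclusions; it would not make the comparison a confirmation of randomisation, and covariate adjustment would not be the remedy.

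A third is that a closed covariate list and an adjustment method are often left to an analysis plan or full protocol, neither of which is shown. This also stands: their absence is not held against the article. The objection is to a purpose that is stated and mistaken, and to stated sections that disagree. An analysis plan faithful to the article would inherit both.

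**Conclusion.** The point holds in a limited form. The protocol gives baseline data a purpose they cannot serve, and it announces a look at confounding that neither its primary test nor its list of planned analyses can accommodate. Whether an adjusted result would appear beside the unadjusted one, and with what standing, is left open.

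The practical size is modest. The 14% to 40% chance of an apparent imbalance rests on three to ten independent tests at 5%, an assumption. The 6% to 10% type I error rests on assumed covariate effects and on unrestricted choice of model, and should be cited only as a worst case. Under the fixed unadjusted test, or under covariates fixed in advance, the level stays at about 5%. The change is worth making because the contradiction is real and pre-specified adjustment is a better method open to the trial at small cost.

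**What to change.** 1. Under Sample size details, delete the purpose of confirming randomisation. Say that baseline characteristics are described by arm, without significance tests. Under Baseline analysis, replace the assertion of similarity with the same statement.
2. Under Main outcome analysis, replace the Kruskal-Wallis test with a model for the binary success outcome, for example logistic. It should allow for teeth clustered in patients (210 / 150 = 1.4 teeth per patient on average) and be adjusted for baseline CBCT lesion diameter, site, and first or second molar. Use these covariates whatever imbalance is seen.
3. In {20b}, say that any other adjusted result is exploratory, so that the three sections agree.

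**Cost.** No new data are needed: lesion diameter and tooth type come from the eligibility assessment, and site is known. It is more than a wording change, because the primary test is replaced. The freedom to adjust the primary result for an unforeseen imbalance is given up. The model also needs enough failures. With two arm terms and three covariate terms there are five coefficients. If 24-month success lay between 70% and 90% (an assumption; the protocol gives no such rate), failures would number 210 × 0.30 = 63 down to 210 × 0.10 = 21, or 12.6 down to 4.2 per coefficient. Near the upper end the model would be thin, so the fitting method should be settled in advance with that in mind.

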### Recruitment {15}

For achieving adequate participant enrolment to reach the target sample size, all new patients meeting eligibility criteria will be given the opportunity to participate in the study. A close coordination is made between the private offices of both co-investigators involved in the study ([name] and [name]) to identify and refer adequately potential participants.

## Assignment of interventions: allocation

### Sequence generation {16a}

Assignments will be prepared by the statistician author of this study ([name]) prior to the trial start. A total of 150 patients (210 teeth) will be recruited and divided into 3 groups at a ratio of 1:1:1, namely, the RCT in a single visit, RCT in two visits with intracanal dressing, and RCT in two visits without intracanal dressing.

Randomization and allocation will be performed before all the clinical procedures.

First, a list of numbers from 1 to 210 will be created, each of the number represents one participant, then the list of numbers was assigned randomly following simple randomization procedures, by using Excel 2019 (Microsoft, Redmond, WA, USA) into three groups of 50 participants (70 teeth) each. Eventually, two columns in the spreadsheet are used, the first column contains the number of the participant (teeth) and the second contains the group to which the participant (teeth) is allocated, determined solely by the software.

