#### Exclusion criteria

Patients may not participate in the study if they are as follows: (1) teeth with extensive coronary destruction that makes direct restoration with composite resin unfeasible, (2) calcified teeth, (3) teeth with incomplete root formation, (4) teeth with persistent exudation, (5) teeth with anatomical complexities that prevent endodontic treatment in a single visit, (6) teeth recommended for endodontic retreatment, (7) teeth with advanced periodontal pocket, and (8) teeth in which foraminal patency is not obtained.

Patients who present a profile that fits to that described in the inclusion and exclusion criteria will then be referred for evaluation by other examiners ([name], [name], and [name], experts in Endodontics for more than 15 years), for confirmation of diagnosis and treatment planning, if necessary. Patients who do not fit the required profile will be forwarded to the health unit of origin. All the steps of interviews and clinical examination necessary to complete the diagnosis will be carried out by the examiners who will perform the treatment.

Patients with systemic diseases (diabetes, transplants, heart disease, liver failure, and kidney failure) and immunodepressed patients are prohibited during the trial as these conditions can affect the oral functions.

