#### First clinical appointment

The first visit will include the following clinical protocol depending on the study group: for the 3 groups (G1, G2, and G3): (1) Anesthesia and caries removal. After local anesthesia with articaine hydrochloride and epinephrine tartrate injection (with 1:200,000 adrenaline [Produits Dentaires Pierre Rolland, Merignac, France]), all decayed tissue from the tooth is removed. (2) Isolation and access preparation. The tooth is isolated with a rubber dam and disinfected, and the pulp chamber will be completely unroofed. (3) Initial irrigation with 5 ml of 5.25% NaOCl. (4) Root canal preparation. The #10 C-Pilot file will be used to perform the glide path along the length of the tooth on the radiograph, irrigated with 2 ml of 5.25% NaOCl, followed by rotary instrumentation with #15/.03, #25/.04, and #30/.05 NiTi files, initially in the cervical and middle thirds, after which the working length with the foraminal locator will be performed. Finally, the instrumentation of the apical third will be performed with the same sequence of NiTi rotary files used previously. (5) The canal will be copiously irrigated in three stages using 10ml of 5.25% NaOCl for each of thirds: cervical, middle and apical, totaling 30ml, followed by a final rinse with 10ml of 5.25% NaOCl stirred with the ultrasonic inserts and 10 ml of 17% EDTA stirred also with ultrasonic inserts. The final rinse will be carried out, according to Haapasalo et al. [21], with 10ml of 70% isopropyl alcohol.

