### Concealment mechanism {16b}

Each number and the group to which a number is allocated will be concealed in sequentially numbered, opaque, sealed, and stapled envelopes. Only investigators can open the envelope, at the moment of intervention, to check the group to which the number is allocated, and perform the interventions according to the instructions of this study.

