### Implementation {16c}

The randomization list is implemented in the software by the study statistician ([name]). Access to the randomization list is limited to the study investigators.

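### Teeth are allocated before treatment, but some exclusions are judged in the opened canal by unblinded operators who can see the randomization list, so exclusion and enrolment can depend on the arm

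*Protocol article*

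**What the plan says.** All references are to the protocol article.

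- **Timing.** Sequence generation {16a}: "Randomization and allocation will be performed before all the clinical procedures".
- **Envelopes.** Concealment mechanism {16b} uses numbered, opaque, sealed envelopes and adds: "Only investigators can open the envelope, at the moment of intervention".
- **List.** Implementation {16c}: "Access to the randomization list is limited to the study investigators".
- **Exclusions.** Exclusion criteria lists "teeth with persistent exudation" and "teeth in which foraminal patency is not obtained". It also excludes teeth whose anatomy makes a single visit impossible.
- **Who judges.** The same section has the treating examiners complete the diagnostic examination. Under Study setting {9}, treatment takes place in the offices of two co-investigators. Who will be blinded {17a} accepts that the dentists know the arm.
- **Common preparation.** First clinical appointment gives one preparation sequence, with ultrasonic activation, for all three groups. Filling or dressing comes only afterwards. Intervention description {11a}, however, names ultrasonic activation among the manoeuvres that vary.
- **Analysis.** Section {20c} plans intention-to-treat with missing counted as failure, a listing of protocol violations, and sensitivity analyses that include maximum bias.

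**The concern.** Randomisation protects the comparison only if entry and retention do not depend on the arm. Both can here. An operator who can read the list may know the next allocation while deciding whether to enrol a borderline tooth. After allocation, the same operator decides whether exudation, patency or anatomy rules the tooth out. The anatomy criterion is worded around the feasibility of one arm, so there is less occasion to invoke it when the tooth is allocated to two visits. The trial is declared a non-inferiority comparison, in which a shift of a few points in either direction can change the conclusion. No later analysis fully restores a comparison whose arms were selected differently.

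**Working it through.** **Step 1: when each criterion can be judged, and by whom.**

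| Criterion | Earliest point at which it can be settled | Relative to allocation as {16a} states it |
|---|---|---|
| Patency not obtained | Negotiation of the canal | After |
| Persistent exudation | In practice, the opened canal | After |
| Anatomy ruling out a single visit | Partly on pre-operative CBCT, partly in the canal | Partly after |

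The decision rests with the treating dentist, who is unblinded ({17a}) and is an investigator with list access ({16c}). Section {18a} also calls the two endodontists and the radiologist who enter data investigators. Read literally, {16c} therefore also strains the blinding of the outcome evaluators.

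**Step 2: what unequal exclusion does to the success rate.** The protocol gives no expected exclusion rate and no reference success rate, so there is no figure to reproduce and every input is assumed. Let P be true success, e the share of teeth excluded after allocation, and q the success those teeth would have had.

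- Dropped or replaced by eligible teeth: (P − e·q)/(1 − e)
- Kept and counted as failures: P − e·q

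Take P = 75% and q = 40%, with exclusions only in the single-visit arm:

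- e = 10%, dropped: (0.75 − 0.10 × 0.40)/0.90 = 0.71/0.90 = 78.9%, or +3.9 points
- e = 10%, failures: 0.75 − 0.04 = 71%, or −4 points
- e = 5%, dropped: (0.75 − 0.02)/0.95 = 76.8%, or +1.8 points
- e = 5%, failures: 0.75 − 0.02 = 73%, or −2 points

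**Step 3: a range, with exclusions in both arms.** Take P = 80% in every arm and 5% excluded in the comparator. Differences are in points, arm with more exclusions minus comparator, from unrounded values.

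| Exclusion | q | If dropped | If failures |
|---|---|---|---|
| 5% vs 5% | 40% or 60% | 0 | 0 |
| 10% vs 5% | 40% | +2.3 | 76 − 78 = −2 |
| 10% vs 5% | 60% | +1.2 | 74 − 77 = −3 |
| 20% vs 5% | 40% | 90.0 − 82.1 = +7.9 | 72 − 78 = −6 |
| 20% vs 5% | 60% | +3.9 | 68 − 77 = −9 |

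The sign depends on how the teeth are counted. The size depends on how unequal the exclusions are, and with equal exclusion there is no shift. For scale, the sample size section uses an effect size of 20%.

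**The case against.** Four arguments can be made for the plan.

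1. **Eligibility comes first.** Study setting {9} and Trial design {8} place eligibility and consent before assignment, and {16b} opens the envelope at the time of intervention, which could mean after the common preparation. But {16a} says before all clinical procedures, and patency cannot be tested before then. At best the sections conflict. Neither reading helps while the investigators can see the list.
2. **The criteria apply to every arm.** This is correct. Patency is met during a preparation common to all groups, so its true frequency should not differ. Anatomy can be judged partly on CBCT, and other examiners may confirm diagnosis and planning. A reader might infer that all three criteria come to light only inside the canal, or that exclusions will differ by arm. The documents support neither; they show only that the design allows a difference.
3. **Intention-to-treat answers it.** A reader might infer that the bias must favour single visit, or that the design contradicts the planned analysis. Neither follows. A bias in favour of single visit needs a rule that removes such teeth, and the article states none. With missing counted as failure, the same inputs work against single visit. But {20c} does not dispose of the problem, because unequal exclusion still moves the result. Section {14} also foresees further recruitment if valid cases are too few, so replacement is conceivable.
4. **The size is assumed.** This stands. The milder case of 10% against 5% gives +1.2 to +2.3 points if the teeth are dropped.

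**Conclusion.** The point holds as a weakness of allocation and concealment. Investigator access to the list is plain in the text and by itself undoes the envelopes. The order of allocation and exclusion is also plain for patency and, in practice, for exudation; for anatomy it is only partial. It follows that exclusion and enrolment can depend on the arm. It does not follow that they will, nor that single visit gains. Under the assumed 75% true success, 10% exclusion confined to single visit and 40% success in the excluded teeth, the single-visit rate reads 78.9% or 71% according to how those teeth are counted. These figures are illustrations, and they leave out any selection at enrolment through a foreseeable allocation.

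**What to change.** 1. **List.** In Implementation {16c}, restrict the list to the statistician or whoever prepares the envelopes. Investigators who enrol, treat or assess get no access.
2. **Timing.** Reconcile {16a} with {16b} so that the envelope is opened only after the part of the first-visit preparation common to all arms, once the intra-operative eligibility criteria are confirmed and recorded. Teeth that fail before that point are screening failures and use no number. First reconcile {11a} with Trial design {8} and First clinical appointment on whether ultrasonic activation varies by arm, since this decides where the common part ends.
3. **Patients with several teeth.** The plan has 150 patients and 210 teeth, so 210 − 150 = 60 teeth are beyond a patient's first, and {16a} treats a number as both participant and tooth. Settle which is the unit of allocation, and confirm the eligibility of all of a patient's study teeth as far as possible before the arm is revealed. Otherwise, if allocation is by patient, the first envelope discloses the arm for the rest.
4. **Teeth already randomised.** Recruitment began in August 2021. Keep teeth later found ineligible in the intention-to-treat set, report them by arm, and show the result both with them counted as failures and with them left out.

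The cost is a short amendment and a site instruction. The drawback is an envelope opened mid-appointment with materials for all arms at hand.
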